### 1.5. Rationale of the study

There is an urgent need to explore therapeutic options for SARS-CoV-2 in order to face the pandemic. In the current guidelines, HCQ has been recommended for treatment of COVID-19 (MOH and Saudi CDC guidelines) due to the early data supporting the use of this drug off-label, especially during the current emergency circumstance and the lack of clear evidence and licensed therapy. The proposed mechanistic antiviral effect of HCQ in COVID-19 is related to its ability to inhibit SARS-CoV2 entry through changing the glycosylation of ACE2 (Angiotensin Converting Enzyme-2) receptor and spike protein and also inhibits post-entry stages of SARS-CoV-2 by blocking the transport of SARS-CoV-2 from early endosomes to endolysosomes, which appears to be a requirement to release the viral genome

On the other hand, favipiravir is a potent inhibitor of viral RNA polymerase. Hypothesis suggests that favipiravir-RTP (favipiravir metabolite) works by blocking polymerase domains, thus preventing incorporation of nucleotides for viral RNA replication and transcription.

Theoretically, combining both agents would result into synergistic effect due to different target sites. However, no previous studies have explored this theory yet. In vitro data demonstrate antiviral effect of both agents against COVID-19. Well conducted/established clinical trials are yet to be developed to evaluate the safety and efficacy of both agents among other agents that believed to have antiviral effect against COVID-19. We believed that both agents have reasonable safety profile if used appropriately. Therefore, combining two potential therapeutic options seems to be an attractive approach, taking into consideration that we are targeting patients with moderate to severe COVID-19 where mortality rate reaches up to 20% in severe cases.

Ongoing clinical trials applying a combination of various potential therapies for COVID-19 is a common approach in these situations, such as lopinavir/ritonavir NCT04303299; tocilizumab NCT04310228; chloroquine NCT04319900; and HCQ NCT04303299, among others, which all have not been completed yet.

The selected combination was based on limited evidence clinically and in vitro on the efficacy of the Favipiravir and Hydroxychloroquine in SARS-CoV-2. The two medications were listed in many guidelines as treatment options and ongoing trials assessing their efficacy and safety. Thus, we want to prove the effectiveness of the combination as therapy.

#### 1.5.1. Research hypothesis

We assume superiority of combination therapy compared to standard of care.

Time to discharge or clinical improvement by 2 points in the standard of care arm is expected to be (median: 11 days). The exact treatment effect from Favipiravir tablets + Hydroxychloroquine is not exactly known but can be approximated using prior clinical studies. A study comparing the effect of Favipiravir to lopinavir/ritonavir on virus clearance has shown a 64% reduction in time to viral clearance in the Favipiravir arm. This was equivalent to a median of 11 days. We assume that clinical improvement might take place a little later to viral clearance and therefore we assume that the treatment arm might result in a minimum clinically meaningful expected reduction of 30% (from a median of 11 days to a median of 7.7 days). This is equivalent to a Hazard ratio of 0.7.

We further assume, that 50% of the patients in the control group will have clinical improvement/ discharged and 70% will have clinical improvement/discharged in the treatment arm.

### 1.5.2. Study Design

This study is a randomized, controlled, open-label trial to evaluate the safety and efficacy of novel therapeutic agents in hospitalized adults diagnosed with COVID-19. It is a multicenter trial that will compare Favipiravir plus Hydroxychloroquine combination (experimental arm) to a control arm.

[figure not shown]

Figure 1: Study Design

### 1.5.3. Dose selection

#### FAVIPIRAVIR DOSING AND ADMINISTRATION

Approved dosage for influenza: 1600 mg BID on day1, followed by 600 mg BID on day 2-5.

Suggested dose for COVID-19 by the manufacturer FFTC and the Japanese guideline: 1800 mg BID on day 1 followed by 800 mg BID on day 2-10

Evidence demonstrating safety and efficacy of higher doses for influenza infection:

1. A placebo-controlled phase I/II study in type A or B influenza patients was conducted (1800 mg BID followed by 800 mg BID for 4 days)

- a. 1800/800 mg BID regimen resulted in  $C_{max}$ = 64.56 mcg/mL, AUC= 446 mcg.hr/mL and associated with significant difference in the time to alleviation of influenza symptoms compared to placebo
2. Two placebo-controlled **phase III** studies on type A or type B influenza patients (1800 mg BID on day1 followed by 800 mg BID on day 2-5)
  - a. The median time required to alleviate influenza symptoms was 84 hr vs 99hr;  $P=0.004$  for favipiravir and placebo group respectively in study 1
  - b. The median time required to alleviate influenza symptoms was 78 hr vs 84 hr;  $P=0.303$  for favipiravir and placebo respectively in study 2

Evidence demonstrating safety and efficacy of higher doses for EBOV infection:

1. Higher concentrations of favipiravir were required to inhibit EBOV than H1N1 based on preclinical studies (150 mg/kg/day vs 100 mg/kg/day in infected mice)
2. In JIKI Trial (prove of concept trial), participants infected with EBOV received oral favipiravir (day0:6,000 mg; day1 to day9:2,400mg/d)
3. Although RNA viral load values and mortality were not significantly different between adults starting favipiravir within <72h of symptoms compared to others. Favipiravir was well tolerated.

### **Oral Tablet:**

Administer 1800 mg (9 tablets) by mouth twice daily for one day, followed by 800mg (4 tablets) twice daily (total days of therapy is 10days)

For patients with Nasogastric tube:

- ☐ Prepare the drug suspension by adding 5 ml of warm water to each tablet (simple suspension method; concentration 40 mg/mL).
- ☐ Slowly inject the suspension into NG tube using a piston.
- ☐ Wash nasogastric tube with 5 mL of water.
- ☐ Follow all precaution during preparing suspension due to teratogenic effect observed in animal studies.

## HYDROXYCHLOROQUINE DOSING AND ADMINISTRATION

No dosage regimen has been approved for HCQ as antiviral agent, however, a robust data derived from pharmacokinetic study confirmed that the dosing regimen below has demonstrated maximum viral killing activity with lowest toxicity treatment of SARS-CoV-2.

### Oral Tablet:

Administer 400 mg (2 tablets) by mouth twice daily for one day, followed by 200mg (1 tablet) twice daily on day 2-5 (total days of therapy is 5 days)

For patients with Nasogastric tube, prepare suspension at bedside as follows:

- Prepare the drug suspension by adding 5 mLs of water to each tablet (simple suspension method; concentration 40 mg/mL).
- Slowly inject the suspension into NG tube using a piston.
- Wash nasogastric tube with 5 mL of water.

There are limited data on hydroxychloroquine teratogenicity. We advice to follow all precaution during preparing suspension

Duration: In one study, **10 days** course of favipiravir was compared to Arbidol and found to be superior in having a higher 7-day clinical recovery rate in patients with COVID-19 and more effective in reducing the incidence of fever and cough. In JIKI Trial, 10 days course of favipiravir was administered

Based on the proposed/hypothetical pathogenesis of COVID-19, the clinical phase is divided into three phases: the viremia phase, the acute phase (pneumonia phase) and the recovery phase. Based on the proposed duration of viremia phase, 10 days treatment is recommended.

[figure not shown]

#### 1.5.4. Selection of endpoints

The selection of those endpoints based on the objectivity and to present the most reliable to assess moderate to severe infection. It is expected that the majority of the cases would be mild. Therefore, the markers used (seven-category ordinal scale), which capture the requirement of hospitalization and Oxygen requirement, reflect the best assessment for such a spectrum.

#### 1.5.5. Benefit/Risk Assessment

##### 1.5.5.1 Known Potential Risks:

- Favipiravir use has been associated with adverse drug reactions including increase of uric acid serum level (~4.8%), diarrhea (~4.8%), decrease neutrophil count (1.8%), and increase in AST and ALT (1.8%, 1.6%) respectively.
- Hydroxychloroquine use has been associated with adverse drug reactions including bone marrow suppression (anemia, leukopenia, agranulocytosis, and thrombocytopenia), QTc prolongation, irreversible retinopathy with retinal pigmentation changes and visual disturbances, nausea, vomiting, diarrhea, and abdominal pain, and skin rash

##### 1.5.5.2 Known Potential Benefits:

- Favipiravir has shown shorter viral clearance time when compared to lopinavir/ritonavir in a study of 80 patients who has Covid-19 (4 days versus 11 days,  $P < 0.001$ ). The Favipiravir arm also showed significant improvement in chest imaging compared with the lopinavir/ritonavir arm, with an improvement rate of 91.43% versus 62.22% ( $P = 0.004$ ).
- Hydroxychloroquine use associated with shorter time to clinical recovery manifested by body temperature recovery and cough remission compared to standard of care group. Improvement in chest CT also has been observed in HCQ group

##### 1.5.5.3 Assessment of Potential Risks and Benefits

The WHO declared COVID-19 as a pandemic on March 12th, 2020^1. The transmission dynamics, disease progression and severity of COVID-19 among human being is under investigation yet to be understood. Looking at the dramatic increase of confirmed cases of COVID-19 in Saudi Arabia and worldwide necessitate exploring therapeutic options that showed promising killing activity against COVID-19 in vitro and have relative safety profiles. Hydroxychloroquine has been used for long time for patients with autoimmune disease. It is well known of its high tolerability profile. Favipiravir has been used as anti-influenza drug for years with good clinical outcomes and have a relative safe profile

## 2. STUDY OBJECTIVES AND ENDPOINTS

### 2.1 Primary Objectives

The improvement of two points (from the status at randomization) on a seven-category ordinal scale\* or live discharge from the hospital, whichever came first.

\*The seven-category ordinal scale consists of the following categories:

8. Not hospitalized with resumption of normal activities
9. Not hospitalized, but unable to resume normal activities
10. Hospitalization, not requiring supplemental oxygen
11. Hospitalization, requiring supplemental oxygen
12. Hospitalization, requiring nasal high-flow oxygen therapy and/or non-invasive mechanical ventilation
13. Hospitalization, requiring ECMO and/or invasive mechanical ventilation
14. Death.

### 2.2 Secondary Objectives

1. To evaluate the progress in clinical status of COVID-19 patients in both arms
2. To monitor the viral shedding duration and PCR test conversion days from positive to negative.
3. Evaluate the safety of investigational therapeutics as compared to the control arm.
4. To evaluate difference in the complications and prognosis of COVID-19 patients between the two groups.

### 2.3 Primary Endpoint

The primary endpoint is the time to clinical improvement, defined as the time from randomization to an improvement of two points (from the status at randomization) on a seven-category ordinal scale or live discharge from the hospital, whichever came first.

## 2.4 Secondary Endpoint

1. Clinical status assessed by the seven-category ordinal scale.
2. The requirement of ICU admission or Mechanical ventilation
3. 28- and 90-days mortality.
4. PCR test negative conversion rate and days from positive to negative\*\*
5. Evaluate the safety of investigational therapeutics as compared to the control arm.
6. Length of hospital stay.
7. Duration of fever.
8. QT prolongation (Daily follow up during the concomitant use of both medications and regularly till Day14)

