#### 4.2 Exclusion Criteria

- 1 Patients who are pregnant or breastfeeding.
- 2 Will be transferred to a non-study site hospital or discharge from hospital within 72 hours.
- 3 Known sensitivity/allergy to hydroxychloroquine or Favipiravir
- 4 Current use of hydroxychloroquine for another indication
- 5 Prior diagnosis of retinopathy
- 6 Prior diagnosis of glucose-6-phosphate dehydrogenase (G6PD) deficiency
- 7 Major comorbidities increasing the risk of study drug including: i. Hematologic malignancy, ii. Advanced (stage 4-5) chronic kidney disease or dialysis therapy, iii. Known history of ventricular arrhythmias, iv. Current use of drugs that prolong the QT interval, Severe liver damage (Child-Pugh score  $\geq$  C, AST > 5 times the upper limit), HIV.
- 8 The investigator believes that participating in the trial is not in the best interests of the patient, or the investigator considers unsuitable for enrollment (such as unpredictable risks or subject compliance issues).
- 9 Clinical prognostic non-survival, palliative care, or in deep coma and no have response to supportive treatment within three hours of admission
- 10 Patient with irregular rhythm or the QTc (corrected QT interval) in the baseline ECG more than 490ms.

- 11 Patient with a history of heart attack (myocardial infarction)
- 12 Patient with a family history of sudden death from heart attack before the age of 50
- 13 Take other drugs that can cause prolonged QT interval
- 14 Patient who is receiving immunosuppressive therapy (cyclosporin) which cannot be switched to another agent or adjusted while using the investigational drug
- 15 Gout/history of Gout or hereditary xanthinuria or xanthine calculi of the urinary tract.
- 16 Serum uric acid level > 2 times upper level of normal associated with symptoms of gout

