### 7.3 Safety monitoring

Site PI should follow on a daily basis all the possible AEs while using the investigational medications and up to day-14. This includes regular monitoring of hematology and blood chemistry. Daily ECG and QT interval monitoring. And LFT every other day. In case of any concerns that might require holding/stopping medication, causality assessment should be done by PI and with a consultation to an independent clinician.

Details of cardiac toxicity monitoring as follow:

1. A baseline ECG before starting then daily ECG after.
2. Daily ECG to be done through day 1-10 or twice daily if the corrected QT interval more than 480ms.
2. Maintain serum level of Mg>1.0 meq, and K>4.5 meq throughout the 10 days of therapy.
3. If the QTc prolonged more than 500ms after starting, stop the medication.
4. Avoid any other QT prolong medication during the regimen.
5. If the patient develops torsades de-pointes, stop the medication immediately, follow ACLS protocol and call the cardiologist on-call.

If you have any query or help, please call for cardiology team in you center.

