## APPENDIX

1. Classification of Adverse Events using the NIH Common Terminology Criteria for Adverse Events (CTCAE), Version 4.0.

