| Definition                                        | A disorder characterized by excitement of psychotic proportions manifested by mental and physical hyperactivity, disorganization of behavior and elevation of mood.         |                                                                                   |                                                                                                                 |                                                                                               |       |
| Electrocardiogram QT corrected interval prolonged | Average QTc 450 - 480 ms                                                                                                                                                    | Average QTc 481 - 500 ms                                                          | Average QTc $\geq$ 501 ms; $>60$ ms change from baseline                                                        | Torsade de pointes; polymorphic ventricular tachycardia; signs/symptoms of serious arrhythmia |       |
| Definition                                        | A finding of a cardiac dysrhythmia characterized by an abnormally long corrected QT interval.                                                                               |                                                                                   |                                                                                                                 |                                                                                               |       |
| Skin and                                          | Asymptomatic or                                                                                                                                                             | Moderate;                                                                         | Severe or medically                                                                                             | Life-threatening                                                                              | Death |

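### Endpoint 8 (QT prolongation) is not defined relative to baseline, and any threshold count would be biased because study-drug patients have more ECGs than controls

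*Protocol*

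**What the plan says.** Protocol Section 2.4, item 8, and the matching item in the Protocol Summary name the endpoint as "QT prolongation (Daily follow up during the concomitant use of both medications and regularly till Day14". Neither gives a cut-off, a grading scale or a comparison with the patient's own baseline.

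Three other parts of the protocol bear on it.

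- **Entry.** Section 4.2, criterion 10, excludes a patient with an irregular rhythm or with "the QTc (corrected QT interval) in the baseline ECG more than 490ms". A QTc of 490 ms or less is therefore no bar to entry.
- **Grading.** The only QT grading scale is the table at the end of the protocol, titled "Classification of Adverse Events using the NIH Common Terminology Criteria for Adverse Events (CTCAE), Version 4.0". Grade 1 is "Average QTc 450 - 480 ms" and Grade 2 is "Average QTc 481 - 500 ms". Only the Grade 3 cell (501 ms or more) mentions baseline, as more than 60 "ms change from baseline".
- **ECG days.** In the flow chart (Section 8), controls have ECGs on D0, D1, D5 and D10. Study-drug patients have D0, D1, D2, the column between D2 and D5, D5 and D10. Section 7.3 Safety monitoring, written around use of the investigational drugs, says: "Daily ECG to be done through day 1-10 or twice daily if the corrected QT interval more than 480ms".

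**The concern.** QTc prolongation is a listed hydroxychloroquine risk (Section 1.5.5.1), so this endpoint should show whether the combination lengthens QTc. Two features work against that.

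First, with no reference to baseline, a count on absolute grades mixes patients who entered with a long QTc with patients whose QTc rose on treatment. A patient at 470 ms at baseline and 468 ms on day 5 would be Grade 1 although the QTc fell.

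Second, any count of patients who ever cross a threshold depends on how often they are looked at. The study-drug arm is looked at more often, and more often still once a QTc exceeds 480 ms. That favours finding prolongation on study drug even if the drugs do nothing.

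**Working it through.** The protocol states no rate or power for this endpoint, so there is no figure to reproduce. Step 1 needs no assumption. All QTc means and SDs in steps 2 to 4 are assumed, because the protocol gives none.

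**1. Overlap.** The entry ceiling is 490 ms. Grade 1 (450–480 ms) lies wholly inside the eligible range, as does 481–490 ms of Grade 2. An unchanged QTc in these bands meets the grade at 0 ms change. Reaching 501 ms needs a rise of at least 501 − 490 = 11 ms.

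**2. Share at or above 450 ms at entry.** For a normal baseline (mean m, SD s) cut off at 490 ms:

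share = [Φ((490 − m)/s) − Φ((450 − m)/s)] / Φ((490 − m)/s)

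| Mean / SD (ms) | Calculation | Share |
|---|---|---|
| 410 / 20 | (0.99997 − 0.97725) / 0.99997 | 2% |
| 440 / 25 | (0.97725 − 0.65542) / 0.97725 | 33% |
| 450 / 20 | (0.97725 − 0.50000) / 0.97725 | 49% |

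Over means of 410–450 ms and SDs of 20–30 ms, the range is 2% to 49%.

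**3. Unequal ECG numbers, no drug effect.** Simulated share with at least one post-baseline QTc of 450 ms or more. Three ECGs is the control schedule in the flow chart; ten is daily ECGs on days 1–10 under Section 7.3.

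| Assumed baseline | Within-patient SD | 3 ECGs | 10 ECGs |
|---|---|---|---|
| Mean 425, total SD 22 | 8–16 ms | 19–27% | 27–49% |
| Mean 440, total SD 25 | 8–16 ms | 43–55% | 53–75% |
| Mean 420–440, between-patient SD 25 | 8–12 ms | 18–48% | 24–61% |

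Scenario by scenario, the gap is 8–22 points for the first two rows and 6–13 points for the third. The flow chart's own study-drug schedule has fewer than ten ECGs, so its gap is smaller but in the same direction.

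**4. Sensitivity with equal ECG days.** Here there are 3 ECGs in each arm, 260 patients per arm, two-sided 5%, the models of the first two rows, and a constant shift on all three ECGs.

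*Threshold count (any QTc of 450 ms or more).* At mean 440, SD 25 and within-patient SD 12, a 5 ms shift moves the share from 48.9% to 57.4%. The standard errors are √(2 × 0.5315 × 0.4685/260) = 0.0438 under the null and √((0.489 × 0.511 + 0.574 × 0.426)/260) = 0.0436 under the alternative. Power = Φ((0.085 − 1.96 × 0.0438)/0.0436), about 49%. Across scenarios, power is about 48–63% at 5 ms and 96–100% at 10 ms. A count of new onset only (baseline below 450 ms) does no better at 5 ms: about 36–58%.

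*ANCOVA on the mean of the three ECGs, adjusted for baseline.* With between-patient variance B and within-patient variance W:

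residual variance = B + W/3 − B²/(B + W)

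The least favourable scenario is mean 440, total SD 25 and within-patient SD 16:

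- W = 256 and B = 625 − 256 = 369
- residual variance = 369 + 85.3 − 369²/625 = 236.5, so the SD is 15.4 ms
- SE of the difference = 15.4 × √(2/260) = 1.35 ms
- power at 5 ms = Φ(5/1.35 − 1.96) = Φ(1.75) = 96%

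A rise of more than 60 ms by noise alone occurs in 0–3% of patients.

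**The case against.** Four objections carry weight.

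- **The protocol never ties endpoint 8 to the CTCAE table.** This stands. The table is there to classify adverse events, and Section 7.3 uses other QTc limits: 480 ms for ECG frequency and 500 ms after starting. A reader might infer that the protocol fixes 450 ms as its definition. It does not, so the overlap is conditional on that choice. The 480 ms limit is also absolute and also lies inside the eligible range. A limit near 500 ms would largely avoid the overlap, but a count on it would still depend on the number of ECGs.
- **A statistical analysis plan may supply the definition.** Missing detail alone would be no finding. But the entry limit, the grading table and the ECG schedules are fixed in this protocol, and they work badly together.
- **Adverse-event handling already covers part of this.** Section 10.3 records onset or worsening, and the formal comparison in Section 9.4 is restricted to SAEs and Grade 3 or higher. Both are true, so the Grade 1–2 overlap does not enter that test. Endpoint 8 is listed separately from it.
- **Randomization balances long baseline values.** This stands, and it limits the harm. It is tempting to say that the background rate hides a real drug effect. With equal ECG days, a simple count keeps 96–100% power at a 10 ms shift and loses it only near 5 ms.

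A reader might also infer that many patients will count without any drug effect. That cannot be said from the documents: the share at entry runs from 2% to 49% on assumption alone.

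**Conclusion.** The point holds in limited form. Endpoint 8 is not set relative to baseline, and the protocol's only QT grading scale overlaps the permitted baseline range. If that scale were used, the overlap would inflate the rate in both arms without itself creating a difference, and would cost sensitivity mainly for shifts of about 5 ms.

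The firmer problem is the ECG schedule. With more ECGs on study drug, any count of patients ever above a threshold is biased towards prolongation on that arm: 6–22 percentage points at 450 ms for 10 ECGs against 3, with no drug effect.

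The overlap itself is arithmetic. The sizes rest on assumed normal QTc distributions, within-patient SDs of 8–16 ms, a constant shift and complete ECGs on all three days. Patients discharged before D10 will lack that ECG, so real power will be somewhat lower for every measure.

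The ECG timing also conflicts internally. Section 7.3 has daily ECGs through day 10, the flow chart marks none between D5 and D10, and the endpoint runs to day 14 although the flow chart has no ECG after D10.

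**What to change.** In Sections 2.4 and 9.4:

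1. Make the main measure of endpoint 8 the change from baseline QTc on the ECG days common to both arms (D1, D5, D10), compared by ANCOVA with baseline QTc as covariate. State whether the D1 ECG falls after the first dose, and how a missing D10 ECG after discharge is handled.
2. Report any categorical count on those same days. Count a patient only if the grade is higher than that patient's own baseline grade, or the rise exceeds 60 ms. Do not require confirmation on the next scheduled ECG: in controls that can be D1 to D5, but on study drug it can be the next day, so the rule would act differently by arm.
3. Reconcile the ECG days in Section 7.3, the flow chart and the day-14 wording of endpoint 8.

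Items 1 and 2 are wording changes: the baseline ECG is already required and no ECG is added. The price is that ECGs outside the common days are listed for safety but do not enter the between-arm comparison, so a brief prolongation seen only on those days is not counted. The count in item 2 makes the rate easier to interpret; the gain in sensitivity comes from item 1. The clinical QTc rules are not affected.
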